## Methods and design

This is a prospective, parallel, cluster-randomised controlled superiority trial with two conditions: [1] an intervention group who will receive MBT and [2] and a control group who receive UC.

The protocol conforms to the Standard Protocol Items: Recommendations for Interventional Trials (SPIRIT) guidelines (Fig. 1). The final reports of the trial will be written following the Consolidated Standards of Reporting Trials (CONSORT) statement.

**Fig. 1 Fig1:**
[figure not shown]
SPIRIT figure

### Recruitment and procedures

In Denmark, local foster care placement agencies are part of the municipalities and employ foster care consultants who provide ongoing support for foster parents. Each foster family is assigned to a foster care consultant in their municipality when a child is placed in the family. This assignment is typically based on the availability of time and the current case load of the foster care consultants. Assignments typically take place in a meeting in which the head of the foster care services has the final say on which foster care consultants are assigned to which foster families. If the availability of time or the discretionary assignment to consultants is related to the effect of treatment, this would introduce selection bias in the estimates of treatment effects. However, based on discussions with municipalities, we believe that the assignments to consultants are primarily based on the availability of time, which, according to the municipalities, is not systematically related to consultant quality or treatment group.

Since each foster care consultant is assigned to a number of foster families we will create a cluster randomized design in which families are randomized to the intervention and control condition based on their assigned foster care consultant witin each municipality. Each participating municipality will be asked to provide an even number of foster care consultants to enter the study. The Danish Center for Social Science Research (VIVE) will receive the names of the foster care consultants and will randomize half of the total number of foster care consultants in each municipality to intervention or control. We will randomize 46 foster care consultants from 10 municipalities across Denmark to MBT training (n = 23) or UC (n = 23). The MBT and control interventions will be offered to 175 foster families by 46 foster care consultants [46 clusters]. The flow chart is presented in Fig. 2.

**Fig. 2 Fig2:**
[figure not shown]
Flow chart

### Allocation

Due to legal, ethical and practical concerns voiced by the municipalities, it was not possible to apply individual randomization of the foster families. Therefore, we employ a quasi-cluster randomized design in which we randomize foster care consultants into two groups: MBT training or UC. By employing a quasi-cluster randomized design, we minimize the risk of spill-over of the intervention to the control families. Usual care is the service that was offered before the trial. When possible, foster families will receive the MBT intervention or the UC from the foster care consultant they are already familiar with. However, in some rare cases, the local placement agency may need to allocate families to an unfamiliar foster care consultant to ensure an even allocation and comparability between the intervention and control group (e.g., referring families on an alternating basis to treatment and control conditions).

### Recruitment

The participating foster care consultants will screen foster families for eligibility into the trial. The foster families will subsequently be invited to participate in the study by the foster care consultant to whom they were referred. Participation is voluntary. The foster care consultants will give oral information about the trial and give an information leaflet on the study to the foster families. Families can also watch a short video about the study. For legal and ethical reasons, foster families in both conditions will be informed of the condition they are allocated to before consenting to participate in the study. Biological parents who still have custody over children will be asked for consent for the child to participate and foster children aged 15 or above will also be asked for consent. Younger foster children aged 4–14 will be informed of the study in an age-appropriate manner. After receiving consent, the foster care consultant will register the foster parents and children through a registration form.

### Participants

Participants are full-time foster families in Denmark with a foster child aged 4–17. Screening for eligibility will be conducted by municipal foster care consultants and consist of five questions designed for the present study in which the foster parents are asked to indicate if the child has any significant emotional, social, or behavioral problems and if they feel as if they are struggling to care for the child or feel a need for further support in caring for the child. Inclusion criteria are: (1) Any kind of foster family (including professional and kinship care) in one of the participating municipalities with at least one full-time foster child aged 4–17 years; (2) the foster child must have been placed with the foster family for at least four weeks; (3) the target child must display emotional, social, or behavioral problems as reported by the foster parents and the foster parents need to report struggling to care for the child or having a need for extra support in caring for the child. The foster family is excluded if any of the following criteria are present: (1) the foster family is already receiving a family therapeutic intervention; (2) the foster family has previously participated in this study with a different child; or (3) the foster child has formally been diagnosed with autism, psychotic disorder, severe language delay or severe substance abuse problems.

If a family has more than one eligible foster child, both children can participate and receive the intervention with their foster parents. However, for this study, we will only collect data from one target child in each family. The target child will be selected by the foster parents, who will be asked to select the child they are most concerned about.

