### Blinding

As the participants will be offered extra support in the intervention group, neither participants nor foster care consultants can be blinded. Data analysts, video coders, and data assessors will be blind to allocation status.

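### Consultants who know their arm screen and invite families, and families consent knowing theirs, so entry to the trial can differ by arm

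*Protocol article*

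**What the plan says.** All references are to the protocol article.

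- **Unit randomised** (Recruitment and procedures): the research centre "will randomize half of the total number of foster care consultants in each municipality to intervention or control", giving 23 consultants per arm.
- **Screening** (Recruitment): "The participating foster care consultants will screen foster families for eligibility into the trial".
- **Invitation** (Recruitment): "The foster families will subsequently be invited to participate in the study by the foster care consultant to whom they were referred".
- **Disclosure** (Recruitment), on legal and ethical grounds: "foster families in both conditions will be informed of the condition they are allocated to before consenting to participate in the study".
- **Registration** (Recruitment): "After receiving consent, the foster care consultant will register the foster parents and children through a registration form".
- **Blinding** (Blinding): "neither participants nor foster care consultants can be blinded".
- **Eligibility** (Participants): five questions designed for the trial. Both the child's problems and the need for help rest on what the carers say; on the latter, "the foster parents need to report struggling to care for the child or having a need for extra support in caring for the child".
- **Target child** (Participants): one child per family supplies the data. "The target child will be selected by the foster parents, who will be asked to select the child they are most concerned about". Where two children are eligible, both may take part and receive the intervention.
- **Primary outcome** (Primary outcome): the CBCL, completed by the foster parents.

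**The concern.** Randomising consultants protects the comparison only if the families who enter under each consultant are found and enrolled in the same way in both arms. Here the person who finds and invites them knows whether MBT is on offer, and the family decides knowing what it will get. The eligibility threshold is a perception (struggling, or wanting more support) that can be asked about and answered differently when therapy is the next step. The arms may then differ at entry in severity, motivation or expected course.

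The article itself gives reasons why the two offers may attract different families. Under Usual care, families in the MBT arm are to have no other therapeutic intervention during the trial, while control families' additional services are simply recorded. In the Discussion, the authors expect that assignment to usual care may be hard to accept. They treat this as an attrition risk, but the same asymmetry acts earlier, at consent.

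At stake is whether a difference in CBCL can be read as an effect of MBT rather than of who was enrolled.

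**Working it through.** **1. Order of events.** No single sentence says that consultants are randomised before they screen. It follows from two statements: families are told their condition before they consent, and they are referred to a consultant who already belongs to a condition. With the Blinding section, this gives: consultant randomised and aware of the arm; consultant screens; consultant invites; family told the condition; family consents; child registered. Every family passes through this sequence.

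**2. Timing of the target-child choice.** No section places the choice before or after disclosure. Registration comes after consent, so the form that names the child is completed when the arm is known. The choice itself may have been made earlier. It matters only in families with more than one eligible child, and the article does not give their share.

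**3. Do the stated safeguards cover this route?**
- Recruitment and procedures discusses selection bias only in how families are assigned to consultants.
- The Discussion concedes that comparability cannot be guaranteed, but attributes this to the lack of strict random allocation. It does not mention screening, consent or choice of child after allocation.
- Intention-to-treat analysis (Statistical analysis) protects against changes after entry. This selection happens before entry.
- Adjustment for the pre-treatment outcome (Statistical analysis) removes observed differences in baseline CBCL. That score comes from foster parents who know their arm, and it does not capture motivation or different regression to the mean.

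**4. The plan's own sample size.** Inputs from Power considerations: d = 0.53 (SD = 1), 23 consultants per arm, power 0.80, alpha 0.05 (taken as two-sided), ICC 0.1.
- Without clustering: n = 56 per arm.
- Families per consultant: m = n(1 − ICC)/(k − n × ICC) = 56 × 0.9/(23 − 5.6) = 50.4/17.4 = 2.90, rounded up to 3.
- Total: 46 × 3 = 138. The stated figure reproduces.

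**5. Illustration of sensitivity.** The documents give no size for the selection difference, so the values of b below are assumptions. Let b be the between-arm difference, in SD of the outcome, that remains after baseline adjustment. The SE is taken from the plan's own sample-size model, which has no covariate.
- At 175 families: m = 175/46 = 3.80; design effect = 1 + 2.80 × 0.1 = 1.280; SE = √(4 × 1.280/175) = 0.171 SD.
- Two-sided type I error = 1 − Φ(1.96 − b/SE) + Φ(−1.96 − b/SE).
- Power if the bias runs against MBT = Φ((0.53 − b)/SE − 1.96).

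| Assumed b (SD) | Type I error | Power if bias runs against MBT |
|---|---|---|
| 0 | 0.050 | 0.872 |
| 0.1 | 0.090 | 0.710 |
| 0.2 | 0.215 | 0.488 |
| 0.3 | 0.418 | 0.269 |

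A larger sample shrinks the SE but leaves b where it is, so recruiting more families does not cure the problem.

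**The case against.** The strongest reply concerns the target child. A reader might infer that foster parents in the MBT arm will put forward the child who seems best suited to therapy, so that the measured child is in effect chosen after the arm is known. The documents do not support that.
- Both eligible children may receive the intervention, so the choice settles who is measured, not who is treated. Most of the supposed incentive disappears.
- The instruction is specific and the same in both arms.
- Screening precedes invitation, and the third inclusion criterion is worded in terms of the target child. The child may therefore often be identified before disclosure, which is fixed only as before consent.

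These points stand, and they reduce the child choice to a secondary route.

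Three further replies have some force. The article calls the design quasi-cluster randomised, explains why, and expects causal conclusions to be tentative. The analysis adjusts for the pre-treatment outcome. The report is to follow CONSORT and a flow chart exists (not shown), so part of the reporting requested here may already be intended.

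None of this reaches the main route. A general caveat about allocation does not tell the reader that screening and invitation are done by people who know the arm. Baseline adjustment is partial for the reasons given above. The legal and ethical reason in Recruitment covers telling families before they consent; it does not require telling them before the screen is complete.

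**Conclusion.** The concern holds for screening, invitation and consent: they are open to identification and recruitment bias, and this applies to every family. For the choice of target child it holds only as a possible secondary route, confined to families with several eligible children and dependent on a timing the article does not state.

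The size and direction of the bias cannot be estimated from the document. A reader might want to express it as a share of d = 0.53, or to conclude that it favours MBT. Either would rest on assumed inputs alone. The table of type I error shows only that modest residual differences would matter at this sample size (0.1 SD gives 0.090, 0.2 SD gives 0.215). It does not show that such differences will occur. The conclusion also rests on the inference that consultants know their arm when they screen, which the described sequence supports. This should be changed, because an inexpensive change in the order of steps reduces the exposure.

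**What to change.** 1. Complete and lock the five screening answers and the named target child on the screening form before the family is told its condition. Disclosure before consent is unaffected.
2. Where feasible, have consultants list eligible families from their current caseload before allocation is released, and invite every listed family. The list can be de-identified if sharing names before consent is not permitted.
3. Report numbers screened, eligible, invited and consenting by arm and by consultant.
4. Compare the screening answers and baseline CBCL by arm, and add a sensitivity analysis that adjusts for the screening answers.
5. State the residual selection as a limitation in these specific terms.

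**Cost.** Steps 1 and 3 to 5 need a small amount of extra form work and reporting. Step 2 may delay the release of allocation slightly, and because MBT consultants are trained after allocation, the list will age while they train. For families who enter later, the screener will still know the arm, and all families will still consent knowing theirs. The fix therefore reduces the bias and makes it visible, but does not remove it.

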### Usual care (control group)

As of 2019, foster parents in Denmark receive intensive support during the first six months of a placement consisting of both coursework and supervision from foster care consultants After the first year of placement, training consists of two one-day training courses annually [47]. As part of the follow-up casework, Danish foster parents receive face-to-face counseling from the local authorities at least once every six months [47]. Given their professional and personal skills, counselors can choose whatever counseling methods or techniques they deem best [48]. According to a large survey of services for foster parents and foster children in 50% of Danish municipalities, 35% of foster parents had not received any counseling within the previous year beyond the basic national requirements [49]. Nineteen percent of foster parents had received group supervision, 23% had received supervision by a trained psychologist or psychiatrist, 13% had participated in a peer group for foster parents, and 15% had received other types of supervision or counseling. Many foster children are, at some point during placement, offered an additional intervention besides the placement, such as treatment for mental health issues [49]. One out of three foster parents in the survey [49] reported feeling partially or entirely unequipped to raise children with mental health issues [48, 49]. During the trial, families who receive the MBT intervention will not receive any other therapeutic interventions (including individual psychotherapy for the child). However, they may still receive the regular and mandatory support services available to all foster families in Denmark, consisting of coursework and the twice-yearly supervision. Foster care consultants will record the additional services and interventions received by the foster families in the control group during the trial. Researchers from VIVE will contact the families to motivate them to participate in the data collection.

### Training and provision of the intervention

Training of foster care consultants consists of a one-day online training course followed by a three-day face-to-face interactive course taught by experienced MBT supervisors from the Anna Freud Center. Throughout the trial, two Danish certified MBT therapists and supervisors will deliver monthly group supervision and three booster sessions to the local MBT therapists to ensure fidelity and high quality of the intervention. In order to measure adherence to the intervention, the MBT therapists will complete a short questionnaire designed for the trial to record the content and participants in each session.

Mentalization-based therapy sessions will take place either in the foster families' homes or in a clinical setting, depending on the wishes of the foster parents, and each family will be offered up to 12 sessions over the course of four months.

For the purpose of this trial, we will consider three sessions as the minimal intervention. Families who only received 0–2 sessions will be considered dropouts.

### Treatment fidelity and adherence to the intervention

Therapists in the MBT group will be asked to fill out an adaptation of the MBT adherence scale [50]. In the usual care group, the control foster care consultants will be asked to complete a questionnaire in which they list the additional services offered to the control group families (beyond the mandatory services received by both groups during the same time period as the MBT intervention.

### Data collection

Data will be collected through web surveys at three timepoints: T1: baseline; T2: post-intervention 20 weeks post-baseline, and T3: follow-up 6 months after the end of the intervention. At T1 and T2, we will also request a short video recording and conduct a home visit. For foster families with foster children aged 4–9 years, the data collection will include two home visits at T1 and T2. The home visit will last about an hour. At the home visit, we will conduct an interview (the Story Stem Assessment Profile (SSAP)) with the foster child. The SSAP will be conducted by graduate students in psychology who are thoroughly trained and receive ongoing supervision from a psychologist (first author) with extensive experience of using story stem methods. During home visits, we will strive to ensure that all children understand the purpose of the assessment and consent to participating. All foster families will also be asked to record a six-minute long video where the primary foster parent and the foster child are together. For foster children 8 years and older, the primary foster parent and the foster child will be filmed in a situation where they have been instructed to plan the perfect day together. For foster children aged 4–7 years, the primary foster parent and the foster child will be filmed in a situation in which they have received no special instructions on what to they should do. Foster parents will be asked to choose an activity, that the foster child usually enjoys and to engage in this activity together with the foster child. In foster families with foster children aged 4–9 years old, the video will be recorded during the home visit. Foster families with older children will be asked to record the video sequence and upload it to a secure data depository hosted by the Danish Agency for Governmental IT Services (Statens IT).

Questionnaire data will be collected through secure online survey databases (defgo and SurveyXact). Foster parents will receive an email with a direct link to the questionnaire through Digital Post, a digital mailbox system providing all Danish citizens with a private email account tied to their social security number. Digital Post ensures secure digital communication between Danish citizens and the public authorities through a secure platform (see https://lifeindenmark.borger.dk/apps-and-digital-services/Digital-Post). Reminders are sent every 7 days. Foster children 10 years and older will receive the questionnaire via a text message. If the foster parent or the foster child needs help to fill out the questionnaire, they will receive a phone call or help from a member of the research team. Foster children will receive a DKK 150 (~ EUR 20) electronic gift card for each of the three data collections. The research team will closely monitor the data collection process. Data will be transferred to secure servers hosted by Statens IT. The data platform conforms to the international ISO27001 standard on how to manage information security. The trial statistician (MA), the principal investigator (MP), and the co-PI ([name]) will have access to the full dataset. We will not collect any biological data. Any adverse events will be monitored during the intervention and reported to the PI.

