## Background

Children in foster care are psychologically vulnerable and show more social, developmental, and behavioral problems than children who live with their family of origin [1, 2]. Many foster children have experienced adverse events before their initial placement, such as physical and emotional abuse and neglect [3]. Furthermore, studies show that children in out-of-home care face significantly higher risks of mental health problems [4, 5], drug and alcohol abuse [6], and suicidal behavior [4, 7, 8] when compared to the general population. Removing a child from their family of origin and placing them in foster care can be a traumatic event for the child and, in some cases, does not improve a child’s life-course [9]. Research is equivocal about the long-term effects of foster care, with studies finding both negative and positive effects on foster children’s developmental trajectories, as measured by behavioral, emotional, and mental health outcomes [9–11].

While a secure, long-term placement is associated with better long-term outcomes for children in foster care [12, 13], placement breakdown is relatively common. Placement breakdown can have devastating consequences for vulnerable children and is costly for society [9, 14]. In Denmark, around 8% of children in foster care experience placement breakdown [15], which typically occurs when foster parents feel unable to care for the child [16]. Many foster parents struggle to manage the complex care needs of the children placed in their care [17]. Therefore, understanding and supporting the needs of foster families is essential if we are to improve the long-term outcomes of children in foster care.

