### Outcomes

Table 1 shows the timing of the administration of measures. Baseline data include foster parent background variables (e.g., age and education) and child variables (e.g., gestational drug/alcohol exposure, age at separation from biological parents, number of previous placements, length of the current placement, and significant mental/physical health problems). T1 is the baseline, T2 is 20 weeks post T1 baseline, and T3 is 6 months post T2.

**Table 1 Tab1:** Outcomes

	Measure	Child age	T1	T2	T3
*Foster Parent measures*					
Background variables for foster parent			√		
Well-being	WHO-5 index		**√**	√	√
Parental Stress	PSS		**√**	√	√
Parental Reflective Functioning	PRFQ		**√**	√	√
*Child measures*					
Background variables for foster children		4–17	**√**		
Child psychosocial adjustment (caregiver)	CBCL	4–17	**√**	√	√
Child psychosocial adjustment (self-report)	SDQ self-report	10–17	**√**	√	**√**
Child Well-being	KIDSCREEN 10-index	8–17	**√**	√	**√**
Child attachment	SSAP	4–9	**√**	√	
*Relationship measures*					
Parental Mind-mindedness	Describe your child procedure		**√**	**√**	
Child Mind-mindedness	Describe your friend procedure	10–17	**√**	**√**	
Coding interactive behavior (video)	CIB		**√**	**√**	
*Other outcomes*					
Placement breakdown	Administrative data			**√**	√

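### Adverse-event monitoring is tied to the intervention period, which ends about six months before T3 and has no defined start or end for usual-care families

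*Protocol article*

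**What the plan says.** Data collection gives the article's only rule on adverse events: "Any adverse events will be monitored during the intervention and reported to the PI". It names no arm, no calendar dates and no route by which events are found.

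The length of the intervention is in Training and provision of the intervention: "each family will be offered up to 12 sessions over the course of four months".

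Follow-up is described twice. Data collection has "T2: post-intervention 20 weeks post-baseline, and T3: follow-up 6 months after the end of the intervention". Outcomes has "T2 is 20 weeks post T1 baseline, and T3 is 6 months post T2".

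The word intervention is used in two ways. Methods and design describes "an intervention group who will receive MBT" and contrasts it with a control group on usual care. Recruitment and procedures, however, says "The MBT and control interventions will be offered to 175 foster families by 46 foster care consultants", which treats usual care as an intervention too.

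On contact in the control arm, Usual care (control group) says: "Danish foster parents receive face-to-face counseling from the local authorities at least once every six months".

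**The concern.** A safety window should mean the same thing in both arms and last as long as the follow-up on which conclusions rest. This one is anchored to a treatment that only one arm receives as a bounded course. Usual care is a continuing service, so even if the sentence is meant to include control families, it does not say when their monitoring starts or stops.

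The window also stops well before T3, although the effect of MBT is to be estimated at T3. The Background lists raised risks in children in out-of-home care, including mental health problems, "drug and alcohol abuse [6], and suicidal behavior [4, 7, 8] when compared to the general population". Nothing suggests that such events fall only within the first four months.

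At stake is the account of adverse events that the final report can give. Events from different or undefined windows in the two arms cannot be set side by side fairly, and events between the end of MBT and T3 would have no stated means of capture. If events come to light mainly through contact with consultants (an assumption, since no route is stated), the arm seen more often would tend to report more of them whatever the true rates.

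**Working it through.** No figure stated in the article is in dispute. The check is a timeline, followed by a comparison of the relevant sections.

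**Timeline**

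Inputs: intervention length of 4 months (Training and provision of the intervention); T2 at 20 weeks (Data collection and Outcomes); T3 six months after the end of the intervention (Data collection) or six months after T2 (Outcomes). Six months is taken as 26 weeks.

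- End of the intervention: 4 × 52/12 = 17.3 weeks after baseline, if sessions start at baseline.
- T3 under Data collection: 17.3 + 26 = 43.3 weeks.
- T3 under Outcomes: 20 + 26 = 46 weeks.
- Time without stated adverse-event monitoring: 43.3 − 17.3 = 26 weeks, or 46 − 17.3 = 28.7 weeks.
- Share of follow-up inside the window: 17.3/43.3 = 0.40, or 17.3/46 = 0.38.

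If the window is stretched to T2, which Data collection labels post-intervention, the gap under Outcomes is still 46 − 20 = 26 weeks. No reading of the dates brings the window near T3.

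**Coverage of the control arm**

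- Methods and design uses intervention group for MBT alone. On that usage the sentence does not reach usual care.
- Recruitment and procedures speaks of MBT and control interventions together. On that usage it does.
- Treatment fidelity and adherence to the intervention asks control consultants to list additional services over the same period as MBT. A matched control window is therefore already in use, but for services and not for adverse events.

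The text supports either reading, and neither gives dates for control families.

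**What is measured in both arms anyway**

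Table 1 schedules the CBCL, SDQ, KIDSCREEN, WHO-5 and PSS at T1, T2 and T3, and placement breakdown from administrative data at T2 and T3. Statistical analysis estimates MBT against usual care at T2 and T3 for the CBCL and a list of secondary outcomes. Placement breakdown is not on that list. Worsening on average would therefore be visible. A few serious events could leave a group mean almost unchanged, so the scales do not replace event reporting.

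**What an arm comparison of events could show**

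With 175/2 ≈ 87 families per arm, 80% power, two-sided 0.05 and an assumed control event rate of 5%, the MBT rate would have to be about 19% without clustering. It would have to be about 21% with a design effect of 1 + (3.8 − 1) × 0.1 = 1.28. For an assumed control rate of 10% the corresponding figures are about 26% and 29%. Only a large excess would be detected, so the comparison should be descriptive.

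**The case against.** The strongest reply is that this is a journal article condensing a fuller protocol that is not shown, and that definitions, forms and procedures for adverse events normally sit there. That stands for definitions and forms, and their absence is not part of this point. It does not answer the point about the window, because the article states one, and that window can be judged as written.

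A second reply is that the trial measures deterioration in both arms through T3. That also stands. A reader might infer that the trial cannot say whether MBT causes harm. The documents do not support this, because a difference in the harmful direction on the CBCL would be estimated at T2 and T3, and placement breakdown is collected.

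A third reply is that power for discrete events is low in any case. That is true, but it argues for descriptive reporting. Unequal ascertainment is a bias, and sample size neither causes nor cures it.

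Three further inferences are tempting and should not be drawn:

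- **That control families are not monitored at all.** The sentence does not exclude them, and the wording in Recruitment and procedures allows a reading that includes them.
- **That MBT families with 0–2 sessions drop out of monitoring.** The article calls them dropouts but does not link that label to adverse events. The intervention period can equally mean the four months, whatever the attendance.
- **That a numerical ratio of contacts, or of falsely differing event rates, can be given.** The MBT figure is a maximum and the usual-care figure a minimum. Usual care (control group) also describes intensive early support and extra supervision for many families. No detection rates are given from which a distorted risk ratio could be calculated.

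**Conclusion.** The point holds in a limited form. The stated window ends about 26 to 29 weeks before T3, and it has no clear meaning for usual-care families, whose coverage is ambiguous. As written, the plan can show average deterioration in both arms but cannot give a fair between-arm account of discrete adverse events.

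The timing rests on the article's own dates, on sessions starting at baseline, and on six months being 26 weeks. The likely direction of distortion, with more events reported under MBT, rests on the further assumption that events surface through consultant contact, and its size cannot be given. This is a cheap improvement to the plan and does not threaten the primary analysis.

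**What to change.** Replace the sentence with a rule that adverse events are collected in both arms over the same calendar window, T1 to T3, by the same method.

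- Add a short, identical set of adverse-event items, asking about the time since the last survey, to the T2 and T3 foster-parent surveys. Send them to all families in both arms, whatever number of sessions they received.
- Base the arm comparison on these items and report it descriptively, with the number of families answering in each arm.
- Report events raised in MBT sessions separately and keep them out of that comparison.
- Reconcile the two statements of T3 in Data collection and Outcomes, so that the end of the window is a single date.

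The cost is amended wording and a slightly longer questionnaire at two existing surveys, with no extra visits. Families know their allocation, so identical items make the opportunity to report equal but do not remove reporting influenced by that knowledge. The report should say so.
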